### Outcome measures

#### Primary outcome

The primary outcome is the difference between intervention and control group in the proportion of patients with *any relevant health-promoting change* (as defined in Table 1) in either smoking behaviour, body weight, physical activity, alcohol consumption, stress level, eating habits or another self-chosen health-related behavioural dimension. The primary outcome will be collected (including confirmatory cotinine testing) 12 months after baseline, and also as secondary outcomes at 1 and 6 months.

**Table 1 Tab1:** Definitions of health-relevant behavioural changes

Behaviour dimension: relevance criterion	Measuring method	References
Smoking: abstinence or reduction of daily number of cigarettes by ≥ 50% from a baseline of ≥ 15 cigarettes	Self-declaration, confirmatory saliva cotinine test at 12 months for quitters	[﻿18﻿, 27]
Body weight: reduction by ≥ 5% if baseline-BMI ≥ 25 kg/m^2^	Standardised home measurements	[28–30, 45, 46]
Physical activity: increase of MVPA by ≥ 90 min per week or increase of LIPA by ≥ 200 min per week, compared to baseline	Recollection-based self-declaration in questionnaire	[31–33]
Alcohol: reduction in number of standard drinks (10 g) per week by ≥ 7 drinks from a baseline of ≥ 14 drinks/week	Recollection-based self-declaration in questionnaire	[35, 36, 47]
Stress: reduction in score of the Perceived Stress Scale (PSS-10, German version) by ≥ 5, compared to baseline	Recollection-based self-declaration in validated questionnaire	[38–41]
Diet: increase by ≥ 10 in score of adapted MedDietScore questionnaire, compared to baseline	Recollection-based self-declaration in validated questionnaire	[44, 48]
Participant’s choice: increase by ≥ 2 levels on a 5 level Likert-type scale (−/0/+/++/+++)	Self-declaration in questionnaire	–

*BMI* body mass index, *LIPA* light-intensity physical activity, *MVPA* moderate- to vigorous-intensity physical activity

The chosen criteria each reflect the lowest level (cut-off point) of a behavioural change with a proven health benefit. For rationales behind the choice of these levels and a justification for choosing “any change” as the binary primary outcome, see the Discussion section.

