#### Secondary outcomes

Additional secondary outcomes are presented in Table 2. All secondary outcomes will be compiled at 1, 6 and 12 months after baseline from the same data already collected for the primary outcome, with the exception of self-efficacy as well as action and coping planning which are collected during the ongoing counselling on Likert-type scales with five levels.

**Table 2 Tab2:** Secondary outcomes

Secondary outcome	
Smoking cessation rates in intervention and control groups among patients with *high intrinsic motivation* to stop smoking	
Smoking cessation rates in intervention and control groups among *all* participants	
Reduction in number of cigarettes per day, compared to baseline	
Weight loss in units of 1 kg, compared to baseline	
Increase in physical activity time per week in units of 5 min, compared to baseline	
Reduction in number of standard drinks per week, compared to baseline, and number of alcohol-free days per week	
Reduction in score of the Perceived Stress Scale (PSS-10, German version), compared to baseline	
Increase in score of translated MedDietScore questionnaire, compared to baseline	
Patients’ degrees of motivation and, if applicable, confidence to achieve and maintain a change in behaviour (self-efficacy)	
If applicable: availability of a plan on when and how to take action (action planning) and existence of a relapse plan (coping planning)	

Additionally, the covariates presented in Table 3 are collected, if applicable.

**Table 3 Tab3:** Covariates

Covariate	Source
Biopsychosocial data of general practitioners (age, gender, experience, type of doctor’s practice, data of medical assistants/nurses)	GP
Biopsychosocial data of patients (age, gender, marital status, educational level, smoking status of partner)	Patient
Characterisation of smoking behaviour (age at onset of smoking, pack-years, number of cigarettes per day, time to first cigarette after wake up, number of previous attempts to stop smoking)	Patient
Participants’ choice of behavioural dimension	GP
Number and duration of coaching/counselling sessions (per patient and in total)	GP
Person conducting the coaching/counselling (doctor or specifically trained medical assistant)	GP
Type of smoking cessation intervention used	GP
Dispense of decision aids	GP
Involvement of partner or peers into the coaching/counselling process	GP
Perceived partner or peer support	Patient

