### Statistical analysis

Baseline characteristics (qualitative and quantitative variables) of GPs and patients will be calculated after recruitment is completed for each arm of the study, with corresponding 95% confidence intervals where applicable.

Crude success rates (i.e. rates of any relevant health-promoting behavioural change and smoking cessation rates) will be compared between intervention and control groups using χ^2^-tests after completion of follow up. As the main analysis, adjustment for cluster effects will then be performed by (multivariate) hierarchical logistic regression with individuals as the unit of analysis, grouping by GP as the random effect and covariates (including the balancing variables) as independent fixed effects.

Changes in outcome measures that do not meet the criteria for clinical relevance defined in Table 1 will be described and presented graphically (density plots, histograms), compared across study arms using χ^2^-tests or *t*-tests and adjusted by random-effects regression models analogous to those used for success rate comparisons, but with the respective behavioural change measures as dependent variables.

All analyses will be conducted following an intention-to-treat (ITT) approach (i.e. outcome data will be obtained from all participants and analysed “as randomised”). Missing values will be replaced by standard multiple imputation (MI) as recommended by Ma et al. [23] for clustered designs with variance inflation factors < 3. Non-responder imputation (NRI; i.e. conservatively treating all missing values as failures) will be used within the scope of sensitivity analyses.

Qualitative information from the process evaluation will be analysed using common coding techniques for qualitative data. A coding tree will be established deductively based on pre-determined domains of interest and refined by inductively adding codes where appropriate. Results will be reported in percentages or categories. Proportions or mean values of different subgroups will be compared using χ^2^-tests or *t*-tests.

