## Discussion

### Justification of the binary primary outcome

#### Any change

To our knowledge, the suggested composite outcome has not been used or validated before. It is largely unknown how—in terms of health benefits—a change in some behaviour dimension A compares with a change in another dimension B, and we know of no standardisation procedure to make sizes of changes comparable over different dimensions. To make matters worse, different behaviour changes are measured on different scales, and health benefits have been associated with absolute changes in some measures but with relative changes in others. We believe that, given these imponderabilities, the binary outcome “any relevant change in any component dimension” keeps the utmost possible intrinsic validity, since, firstly, the validity of the individual relevance criteria has been demonstrated and, secondly, no further assumptions on interaction or comparability of different behaviour changes are needed. Moreover, while using a dichotomous primary outcome measure inevitably incurs some loss of information, the study findings will be all the more meaningful for clinical care, provided that a statistical difference will be found [24]. The loss of information will be compensated for by analysing secondary outcomes.

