#### Stress level

The Perceived Stress Scale (PSS-10) [38] was chosen for its widespread recognition and frequent use in psychometric research, for the availability of a free and validated German translation, and for its briefness and practicability. Furthermore, the PSS-10 is one of only few scales for which we were able to find satisfactory data describing quantitatively the score changes after stress relief interventions or the association between changes of the score and health outcomes.

Two relatively small studies by Wiegand et al. [39] and Kirby et al. [40], both carried out in non-clinical community settings and with baseline PSS-10 scores of approximately 24 (scale ranges from 0 to 40), found mean decreases in the total PSS-10 scores by about 6.3–9 after stress management interventions of 14 weeks or 10 days, respectively, and about 4.1–5 in the control groups. Based on these data we consider a score reduction by at least 5 as a relevant change. This choice gets some empirical support from results of validation studies that established standard deviations in the order of our criterion [41] and showed that our criterion roughly corresponds to the mean difference between psychiatric outpatients and the general population [42].

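### As worded, the between-arm comparison of behavioural changes is restricted to changes below the Table 1 cut-offs, which selects on the outcome and conflicts with Table 2 and the ITT rule

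*Protocol article*

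**What the plan says.** All references are to the protocol article.

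- **Statistical analysis, second paragraph:** success rates (any relevant change, and smoking cessation) are compared crudely and then by hierarchical logistic regression.
- **Statistical analysis, third paragraph:** this turns to the change measures: "Changes in outcome measures that do not meet the criteria for clinical relevance defined in Table 1 will be described and presented graphically". They are then compared across arms by χ²-tests or t-tests. A modelling step completes the rule: "adjusted by random-effects regression models analogous to those used for success rate comparisons, but with the respective behavioural change measures as dependent variables". The rule is therefore inferential as well as descriptive.
- **Statistical analysis, fourth paragraph:** all analyses follow intention to treat: "outcome data will be obtained from all participants and analysed “as randomised".
- **Secondary outcomes, Table 2:** the continuous outcomes carry no restriction by size of change, for example "Reduction in number of cigarettes per day, compared to baseline" and "Reduction in score of the Perceived Stress Scale (PSS-10, German version), compared to baseline".
- **Discussion, Any change:** the binary primary outcome is defended partly because "The loss of information will be compensated for by analysing secondary outcomes".

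**The concern.** The relative clause in the third paragraph defines what is analysed: changes that fall short of the relevance criterion. Whether a change falls short is known only after randomisation and is itself the outcome. If the intervention works in a dimension, more intervention than control patients cross the cut-off there and drop out of the comparison. The two remaining groups are then no longer those created by randomisation, and the patients who changed most are missing from both, in unequal proportions.

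At stake is the interpretation of the continuous secondary outcomes: cigarettes, weight, activity, alcohol, stress and diet. They are meant to show how far behaviour moved beyond a yes/no success. A comparison that discards the larger changes cannot do that, and a null result from it could be misread as no effect. If the sentence stays ambiguous, the choice between two analysis sets with materially different results also remains open when the data are seen.

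**Working it through.** **Plan's own figures.** The article gives no figure for the change analyses. Its sample size for the primary outcome reproduces with the unpooled formula: (0.40·0.60 + 0.15·0.85)·(1.960 + 1.282)²/0.25² = 61.8, hence 62 per arm. It is not in dispute. I use it only to confirm the 40% and 15% rates.

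**Model.** Change X is normal with mean μ and SD σ, and the treatment shifts μ. Patients with X below the cut-off c are kept. With a = (c − μ)/σ,

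E[X | X < c] = μ − σ·φ(a)/Φ(a), and the proportion kept is Φ(a).

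**1. PSS-10.** The criterion is "reduction in score of the Perceived Stress Scale (PSS-10, German version) by ≥ 5, compared to baseline", so c = 5. The Stress level section reports two studies that "found mean decreases in the total PSS-10 scores by about 6.3–9 after stress management interventions of 14 weeks or 10 days" and falls of about 4.1–5 in their control groups. It puts the SDs from validation studies at about the size of the criterion. I read that as the SD of the score. No SD of change is given, so σ = 5 is an assumption, with a range of 4 to 8.

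Lower means, 6.3 versus 4.1, σ = 5:
- Intervention: a = −0.26, φ/Φ = 0.3857/0.3974 = 0.970, mean of those kept 6.3 − 4.85 = 1.45; 40% kept.
- Control: a = 0.18, φ/Φ = 0.3925/0.5714 = 0.687, mean of those kept 4.1 − 3.43 = 0.67; 57% kept.
- The full difference of 2.2 becomes 0.78, a loss of 64%.

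Other results at c = 5:

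| Means | σ | Full difference | Sub-threshold difference | Lost |
|---|---|---|---|---|
| 6.3 vs 4.1 | 8 | 2.2 | 0.79 | 64% |
| 7.65 vs 4.55 (mid-range) | 5 | 3.1 | 0.99 | 68% |
| 9 vs 5 | 5 | 4.0 | 1.15 | 71% |
| 9 vs 5 | 4 | 4.0 | 1.09 | 73% |

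The article gives ranges and does not pair them here. The cross-pairings (9 vs 4.1 and 6.3 vs 5) at σ = 4, 5 and 8 give losses of 65–71%, inside the same 64–73% band.

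**2. Precision, mid-range means, σ = 5.** Of 200 patients, 100 per arm, 75 remain after the 25% dropout. The restriction keeps about 75·0.298 = 22 intervention and 75·0.536 = 40 control patients. Power at two-sided 5% falls from 0.97 to 0.27, ignoring clustering. With the article's design effect, 1 + 3·0.04 = 1.12, it falls from 0.95 to 0.25.

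**3. Calibrating to the proportion crossing the cut-off (σ = 1, c = 0).**

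| Crossing, intervention vs control | Full shift (SD) | Sub-threshold (SD) | Lost |
|---|---|---|---|
| 40% vs 15% | 0.78 | 0.41 | 47% |
| 20% vs 10% (assumed) | 0.44 | 0.28 | 35% |
| 10% vs 5% (assumed) | 0.36 | 0.28 | 24% |

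The 40% and 15% are the design rates for the seven-dimension composite, so applying them to one dimension is an assumption. Rates in a single dimension may well be lower.

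**4. Limits of the model.** In Table 1 the cigarette-reduction, weight and alcohol criteria also require a minimum baseline (15 cigarettes a day, BMI 25, 14 drinks a week). Patients below it remain in the set however much they reduce, apart from those who stop smoking altogether. For these three dimensions the simple cut-off is only an approximation, and the set mixes patients who could not meet the criterion with patients who did not.

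**The case against.** The strongest reply is that this is loose drafting. The word *only* does not appear. The sentence follows the paragraph on success rates, and it can be read as moving from the binary outcome to change on the underlying scales whether or not the cut-off is reached. Density plots and models with the change as dependent variable fit that reading. So do Table 2, the ITT statement and the Discussion, which all point to analysis of the whole sample. The article is also condensed, and model detail for each secondary outcome normally sits in the analysis plan.

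Much of this stands as an account of intent, and a reader should not infer that the authors decided to exclude responders. It does not rescue the sentence. The benign reading requires ignoring the relative clause, and a rule that is stated and gives a biased comparison is not the same as omitted detail. Both readings need the same correction.

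The reply is also right about size. A reader might infer that the restriction removes most of the treatment difference in every continuous outcome. The documents do not support that. The losses above 60% come from the PSS-10 example, whose means are from two relatively small studies of dedicated stress programmes in non-clinical settings. They are not expectations for this trial, where patients choose among dimensions. With fewer patients crossing the cut-off, the loss is about a quarter to a half.

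**Conclusion.** The point holds as a fault in the stated rule. Taken literally, the third paragraph of Statistical analysis restricts the between-arm tests and random-effects models to changes below the Table 1 criteria. It thereby conditions on a post-randomisation outcome and conflicts with Table 2, with the ITT statement and with the purpose given for the secondary outcomes.

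Under a normal-shift model the attenuation is roughly a quarter to 70%, depending on the dimension: 64–73% for PSS-10, 47% at 40% versus 15% crossing, and 24–35% at the lower assumed rates. These figures rest on normality, a pure shift, an assumed SD of change, exclusion dimension by dimension, and crossing rates that the article does not give by dimension. They show the order of the bias and do not forecast it.

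The primary outcome, its hierarchical logistic model, the sample size and the smoking cessation comparisons do not depend on this sentence and are unaffected.

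**What to change.** Replace the opening of the third paragraph of Statistical analysis with wording such as: *Changes in all continuous Table 2 measures will be described and compared between arms in all participants as randomised, whether or not the Table 1 criterion is met.* The tests and random-effects models can stay as they are. If sub-threshold changes are of interest in themselves, show them descriptively, without a between-arm test.

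The cost is one sentence, to be settled before outcome data are analysed. It needs no new data, no extra patients and no change to the primary analysis.

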## Methods/design

### Study design and setting

A cluster randomised controlled trial (randomisation on the GP level) will be conducted with 60 German-speaking GPs from the northern part of Switzerland (see Fig. 1 for the study flow chart). The design and methodology of the study are partly based on experiences gained from a previous trial carried out by the last author in eastern Switzerland [8]. The SPIRIT checklist for this protocol can be found in Additional file 1.

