#### Process outcomes

In parallel to the ongoing study, additional data will be collected regarding the implementation, effectiveness and cost–benefit ratio of the intervention with the aim of forming a solid basis for decision about further promotion and dissemination of the Health Coaching programme. The results of the evaluation are expected to lead to more profound insights into the methodology of the intervention, in how to optimally train the multiplicators and into factors influencing the acceptance of the intervention by the target population. Furthermore, the process evaluation comprises an analysis of the costs generated by the intervention.

We chose the RE-AIM framework [16] by Glasgow et al. [17] as a comprehensive concept within which to address these objectives.

Process outcomes (Table 4) will be evaluated based on case report and log files used within the actual trial and also using additional methodology specific to the respective questions: semi-structured interviews, questionnaires, telephone interviews and focus group sessions.

**Table 4 Tab4:** Process outcomes

Process evaluation outcome	Source
Reach: proportion and representativeness of individuals receiving the intervention (individual level)	
Rate of smokers among the GP's patients	GP
Rate of smokers invited to participate	GP
Rate of refusals, with reasons	GP
Patient dropout rate, with reasons	GP
Patients’ characteristics and representativeness	See covariates
Efficacy: success rates of the intervention (including satisfaction outcomes) under study conditions (individual level)	
Behaviour change rates	See outcomes
Changes in self-efficacy and planning	See outcomes
Patients’ current overall satisfaction with coaching programme	Patient
Adoption: proportion and representativeness of organisations willing to adopt the intervention, with consideration of enablers and barriers to adoption (organisational level)	
Rate of GPs invited to participate	SC
Rate of refusals, with reasons	SC
GP dropout rate, with reasons	SC
GPs' characteristics and representativeness	See covariates
Involvement of medical assistants/nurses	See covariates
Assistants'/nurses' characteristics	See covariates
Assessment of GPs' precognitions, understanding of coaching/counselling concept and increase in knowledge and skills, evaluation/rating of coaching/counselling concept and structure of training, recommendation to colleagues	GP
Time required for coaching/counselling	See covariates

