Rating of coaching/counselling tools in matters of usefulness and manageability, enabling factors and barriers in coaching/counselling as perceived from practical experience	GP
Overall assessment: benefit for daily practical work, most crucial aspects (success factors and pitfalls), suggestions for improvement, overall satisfaction	GP
Implementation: extent to which the intervention is implemented under real-world conditions—patient adherence (individual level) and adherence of staff to study protocol (organisational level)	
Number of coaching/counselling sessions per patient	See covariates
GPs'/assistants'/nurses' attitudes, competences and (mental) barriers towards/in/to delivering the interventions	GP
Changes in contents or duration of coaching/counselling elements during the ongoing trial	GP
Completeness/integrity of data reported by GPs	SC
Costs arising from expenditure of coaching time	SC
Maintenance: sustainability of intervention over time—relapse rates (individual level) and integration of intervention into institutional routine (organisational level)	
Upholding of beneficial behaviour at 12 months after end of follow up	Patient
Number of GPs trained in HC until 12 months after end of follow up	HC registry
Number/frequency and quality/intensity of coaching over a period of 12 months beyond follow up	GP
Response among experts and media coverage	Experts, media
Maintenance costs	GP

*GP* general practitioner, *HC* Health Coaching programme, *SC* study centre

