### Sample size calculations

For sample size calculations with respect to the superiority hypothesis, we assume success rates of 40% in the intervention and 15% in the control group. The 40% assumption is based on results from the preceding study [8] in which one out of two participants declared subjective improvements in their self-chosen behavioural dimension after coaching. The success rate of 15% in the control group is the sum of a 10% smoking cessation rate achievable by state-of-the-art smoking cessation counselling according to Comuz et al. [18] plus an estimated 5% of “spontaneous” effects of smoking cessation counselling on one of the other behavioural dimensions. Using *α* = 5% (two-sided) and *β* = 10% we calculated a sample size of 62 participants per equally sized study arm [19] or 2 · 62 / (1 – 0.25) = 166 participating smokers in total after factoring in a dropout rate of 25%. To reflect the correlation structure of the clustered design, an intra-cluster correlation coefficient (ICC) of 4% was assumed, which is slightly higher than corresponding values suggested by Parker et al. [20], in order to account for rare cases of GPs from the same group practice. This assumption is also backed by (unpublished) calculations from the previous study [8] with similar cluster structure and outcome. Correction for the cluster effect increases the sample size to 166 · [1 + (4 – 1) · 0.04] = 186 or roughly 200 patients, assuming that a general practitioner is able to recruit four patients. Finally, allowing for a dropout rate of 15% among general practitioners, 186 / 4 / (1 – 0.15) = 56 (rounded to the next higher even number) or roughly 60 general practitioners must be recruited to detect the expected difference in the primary outcome between the two study arms.

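### Process-evaluation comparisons of patient-level data are given only ordinary χ² and t-tests, so between-arm p-values there are somewhat too small

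*Protocol article*

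**What the plan says.** The allocation unit is the GP (Protocol article, Study design and setting): "A cluster randomised controlled trial (randomisation on the GP level) will be conducted with 60 German-speaking GPs". The Sample size calculations section accepts the consequence: "To reflect the correlation structure of the clustered design, an intra-cluster correlation coefficient (ICC) of 4% was assumed".

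The Statistical analysis section then treats three groups of comparisons differently:

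- **Success and cessation rates.** Crude rates "will be compared between intervention and control groups using" χ² tests. The section continues: "As the main analysis, adjustment for cluster effects will then be performed by (multivariate) hierarchical logistic regression with individuals as the unit of analysis", with GP as the random effect.
- **Changes in outcome measures that fall short of the relevance criteria.** χ² or t-tests are used, and the comparisons are also "adjusted by random-effects regression models analogous to those used for success rate comparisons".
- **Process evaluation.** "Proportions or mean values of different subgroups will be compared using" χ² or t-tests. No adjusted model is named, and the subgroups are not defined.

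Table 4 (Process outcomes) mixes levels. Some items are per patient, for example "Patients’ current overall satisfaction with coaching programme", refusals, patient dropout and the number of sessions. Others come from the GP as a single respondent, for example "Overall assessment: benefit for daily practical work, most crucial aspects (success factors and pitfalls), suggestions for improvement, overall satisfaction".

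**The concern.** An ordinary χ² or t-test treats every patient as independent. If patients of one GP resemble each other and whole GPs are allocated to an arm, the between-arm difference varies more than the test assumes, and the p-value is too small on average. The protocol recognises this for its outcomes and plans a suitable model for them, but does not carry that model over to the process evaluation.

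Some within-GP correlation is plausible for the patient-level process items. According to the Intervention section, the GP, or an assistant whom the practice has had trained, delivers the sessions, and their number is agreed between patient and physician. The process results also have a stated use: the Process outcomes section wants them to inform decisions on promoting and disseminating the programme. At stake is a modest overstatement of the evidence for between-arm differences in acceptance, retention or delivery.

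**Working it through.** **Inputs from the protocol.** ICC 0.04; four patients per GP in the sample size formula; success rates 40% and 15%; two-sided α 5%; β 10%; patient dropout 25%; GP dropout 15% (all Sample size calculations); 200 patients and 60 GPs, so 200/60 = 3.33 patients per GP (Patient recruitment and allocation).

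**1. The plan's own figures reproduce.**
- Per arm: (1.960 + 1.282)² × (0.40 × 0.60 + 0.15 × 0.85) / 0.25² = 61.8, so 62.
- Patient dropout: 2 × 62 / 0.75 = 165.3, so 166 as an even total.
- Clustering: design effect DE = 1 + (4 − 1) × 0.04 = 1.12, and 166 × 1.12 = 185.9, so 186.
- GPs: 186 / 4 / 0.85 = 54.7, so 56 as an even number.

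The plan's allowance for clustering is therefore a DE of 1.12.

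**2. Effect of leaving this allowance out of a between-arm test.** The true standard error is √DE times the one used. At DE = 1.12, √1.12 = 1.058, so the correct standard error is 5.8% larger than the one used. The actual type I error of a nominal 5% test is 2 × [1 − Φ(1.96 / √DE)], with DE = 1 + (m − 1) × ICC for m patients per GP:

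| ICC | m | DE | Type I error |
|---|---|---|---|
| 0.04 (protocol) | 4 | 1.12 | 6.4% |
| 0.04 (protocol) | 3.33 | 1.093 | 6.1% |
| 0.04 (protocol) | 3 | 1.08 | 5.9% |
| 0.10 (assumed) | 3 | 1.20 | 7.4% |
| 0.20 (assumed) | 3 | 1.40 | 9.8% |
| 0.30 (assumed) | 3 | 1.60 | 12.1% |

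Three patients per GP is also what remains of four after the protocol's 25% dropout (4 × 0.75 = 3), which is relevant to items that patients report themselves.

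**3. Check by simulation.** Beta-binomial data were generated with 25 GPs per arm, four patients each, a 30% event rate and 100,000 runs. The unadjusted between-arm test rejected in 5.2% of runs with practically no clustering, 6.6% at ICC 0.04 and 8.7% at ICC 0.10. This agrees with the formula (6.4% at 0.04, 8.6% at 0.10).

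**4. Subgroups within GPs.** If a subgroup factor splits each GP's patients two against two, the GP effect cancels from the difference. The same simulation then gives 4.6% at ICC 0.04 and 3.9% at ICC 0.10. Here the ordinary test is slightly conservative, and its p-values are too large.

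**5. Refusals.** These are counted among smokers invited, who outnumber those recruited by an amount the protocol does not give. If one in two accepted, about eight would be invited per GP; then DE = 1 + 7 × 0.04 = 1.28 and the error is 8.3%. The acceptance rate is an assumption.

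**The case against.** The strongest objections concern scope.

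- The section already deals with clustering where it matters most. The χ² test of success rates is labelled crude, the hierarchical model is declared the main analysis, and the change measures also get random-effects models. This stands. A reader might infer that the trial's main conclusions rest on invalid p-values; the text does not support that.
- The process sentence closes a paragraph that opens with qualitative coding, so it may chiefly concern coded interview and focus-group material. The protocol does not say outright that satisfaction, sessions, dropout or refusals will be tested this way. This stands in part. The sentence is worded generally, it is the only test rule given for process data, and the paragraph opens by naming the process evaluation.
- Many Table 4 items have one record per GP or are single overall rates, and the behaviour-change and self-efficacy items refer back to the trial outcomes. This stands: the number of affected items is small.
- A reader might infer that all process p-values are too small. Because the subgroups are undefined, this does not follow; splits within GPs push the error the other way.
- ICCs of 0.1 to 0.3 appear nowhere in the protocol. This stands, and only the figures at ICC 0.04 use a documented ICC.
- Detail on process analyses is often left to an analysis plan that is not shown. This does not remove the point, because the article does state a choice of test and that choice conflicts with its own correlation assumption.

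**Conclusion.** The point holds in a narrow form. For patient-level process measures compared between arms or between groups of GPs, the only stated tests ignore clustering that the protocol itself assumes. At its ICC of 0.04 the type I error is about 6.4% with four patients per GP and 5.9% to 6.1% with 3 to 3.3, an excess of roughly 0.9 to 1.4 percentage points. These figures assume equal cluster sizes and that the outcome ICC carries over to process measures. For items measured on recruited patients, a materially larger error needs a larger ICC, on which the protocol is silent; for refusals it could also come from larger clusters.

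Comparisons within GPs, data with one record per GP, and the primary, cessation and behaviour-change conclusions are outside the point. The severity is minor.

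**What to change.** Add one or two sentences to the Statistical analysis section:

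- Patient-level process measures compared between arms or groups of GPs are analysed with the GP random-intercept model already planned for the outcomes (logistic or linear as appropriate), or with a cluster-robust test.
- Ordinary χ² and t-tests are kept for data with one record per GP.
- The crude χ² and t-tests of trial outcomes are labelled descriptive, so that each outcome has one inferential p-value.

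It would also help to state which subgroups are meant, since the direction of the error depends on it.

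The cost is a little more analysis code and slightly larger p-values for some process comparisons. Data collection, sample size and the main analysis do not change.
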